#### Primary endpoint

The primary clinical efficacy endpoint is cure rate, i.e. proportion of patients with complete lesion healing without recurrence and without excision surgery 12 months after treatment initiation, in the PP PCR-positive population.

#### Secondary endpoints

Secondary endpoints include:Derive and compare main PK parameters for RIF, CLA, and AMX for the two groups (RC8 and RCA4) at a steady state. These include area under the curve (AUC), trough concentration (*C*_*τ*_), maximum observed drug concentration (*C*_max_), time to maximum observed drug concentration (*t*_max_), and elimination half-life (*t*_1/2_).Characterize the POPPK in BU patients randomized on RCA4 and derive population PK parameters of interest, such as apparent Clearance (CL/F), apparent volume of distribution (V/F), and absorption rate (Ka), together with potential covariates of interest. This will involve investigating inter- and intra-subject variability for RIF and AMX.Rate of complete lesion healing without recurrence and without excision surgery, 12 months after start of treatment in the ITT-E PCR-positive, PP CD, and ITT-E CD populations.Rate of complete lesion healing without recurrence and without excision surgery 12 months after start of treatment by category (I, II, and III) lesions analysis in all ITT-E and PP populations.Recurrence rate within 12 months of treatment initiation in all ITT-E and PP populations.Treatment discontinuation rate in all ITT-E and PP populations.Treatment compliance rate in all ITT-E and PP populations.Rate of paradoxical response within 12 months of treatment initiation in all ITT-E and PP populations.Median time to healing after treatment initiation in all ITT-E and PP populations.Proportion of patients with reduction in lesion surface area within 12 months of treatment initiation in all ITT-E and PP populations.Interval between healing and recurrence within 12 months of treatment initiation in all ITT-E and PP populations.Incidence of all AEs, SAEs, and serious unexpected suspected adverse drug reactions (SUSAR) within 12 months of treatment initiation among treatment arms in all SP, ITT-E, and PP populations.Rate of median bacterial clearance among treatment arms in the bacterial clearance sub-study population.Rate of patients with BUFLS improvement within 12 months of treatment initiation among treatment arms in all ITT-E and PP populations.

### Data management

#### Data collection and management

Source documents include subject hospital/clinic records, physician’s and nurse’s notes, appointment book, original laboratory reports, digital pictures of wound lesions, and special assessment reports, signed informed consent forms, and subject screening and enrolment logs. In order to ensure data quality, a uniform hard copy CRF (in French) will be designed for use at all the study sites. A CRF for each randomized patient will be completed at each study visit.

Study site staff and the PI in each site will be responsible for evaluating the CRFs for completeness before entering into an electronic clinical database. Once entered, data will be collected and sent on an ongoing basis to the DMMC for cleaning. The central electronic database will be based on the Open Data Kit platform, with data encrypted in transit and at rest in ODK Cloud, where data are backed up continuously [https://getodk.org/]. The data manager will review the data for discrepancies and missing data. The site will then be informed to make any required corrections and/or additions. Moreover, CRFs and source documents will be monitored by the Monitoring Team (MT) (ISCIII). Discrepancies noted either by the monitor or data centre will be queried to the site PI. The trial data will be stored in a computer database maintaining confidentiality in accordance with national data legislation and Good Clinical Practice (GCP). The data management plan will outline the procedures and guidelines to ensure data quality.

Patient information will be stored in a high-security computer system and kept strictly confidential. Confidentiality will be ensured utilizing a patient identification code number corresponding to treatment data on the computerized files.

#### Access to data, monitoring, and audits

Monitoring visits to the trial site will be made periodically by the sponsor representatives and/or designated monitors to ensure that GCPs and all aspects of the study protocol are being followed. The monitoring visits will provide the opportunity to evaluate the progress of the study, verify the accuracy and completeness of CRFs/SAE forms, resolve any inconsistencies in the study records, and ensure that all protocol requirements, applicable regulations, and investigator’s obligations are being fulfilled. At least four types of visits are planned: pre-study, study start, during the study, and study end. During the actual recruitment period (years 2 and 3 of the study), visits will be performed at least twice a year.

Source documents and SAE forms will be reviewed for verification of consistency with data on CRFs. Site investigators will facilitate direct access to all CRFs/SAE forms, medical records, laboratory work sheets and to assess the status of drug storage, dispensing, and retrieval at any time during the study. The corresponding source documents for each subject will be made available provided that subject confidentiality is maintained in accord with local regulations.

It will be the monitors’ responsibility to inspect the CRFs/SAE forms at regular intervals throughout the study, to verify the adherence to the protocol and the completeness, consistency, and accuracy of the data being entered on them.

### Statistical analysis

#### General considerations

The rationale for selecting the non-inferiority study design is that, considering the efficacy of the standard treatment (RC8) of as high as 95.9% (first quartile–third quartile 91.3–98.5%) [34] (*ClinicalTrials.gov Identifier: NCT01659437*) or 96% in a 14-week delayed-decision to surgery group [32] (*ClinicalTrials.gov identifier: NCT01432925*), whether the experimental treatment (RCA4) could be equal or better is not the relevant question. Rather, the main consideration is to what extent shortening the treatment to 4 weeks with RCA4 could be inferior to the current standard of care.

#### Sample size

The sample size calculation is based on clinically meaningful non-inferiority between the standard treatment group (RC8) and the investigational treatment group (RCA4), as suggested by key informants, experts in BU case management [34] (*ClinicalTrials.gov Identifier: NCT01659437*); [32] (*ClinicalTrials.gov identifier: NCT01432925*). Assumptions are:Equal cure rate of 95.9% for PCR-confirmed patients the two arms (RC8 & RCA4). − 10% non-inferiority margin.2.5% one-sided alpha level.

Under these assumptions, the study would require 62 PCR-confirmed patients per treatment arm to reach 80% power (total sample size = 124). It is estimated that 5% of PCR-confirmed patients will be lost-to-follow-up, so 66 PCR-confirmed patients are needed in each arm (or 132 in total) to achieve the required 62 evaluable patients. Pobè treatment centre reports a PCR confirmation rate of approximately 95% in patients clinically diagnosed as very likely or likely to have BU following the WHO scoring criteria. Therefore, approximately 70 clinically diagnosed BU patients will need to be recruited in each arm (or approximately 140 in total) to reach the 66 PCR-confirmed. Recruitment will continue until at least 66 PCR-confirmed patients have been randomized to each arm.

Recruitment rates will be monitored closely and, if it is feasible within the timeframe available, the study will be extended to achieve 90% power. For 90% power, based on the assumptions above, the study would require data from 83 evaluable PCR-confirmed patients per treatment arm (or 166 in total). Allowing for 5% lost-to-follow-up means 88 PCR-confirmed patients are needed in each arm (or 176 in total). To achieve this, approximately 93 clinically diagnosed BU patients will need to be recruited in each arm (or approximately 186 in total). In this scenario, recruitment will continue until at least 88 PCR-confirmed patients have been randomized to each arm.

#### Efficacy analysis

Primary efficacy analysis will be determined for the PP PCR-positive population. The adjusted estimate of the difference (expressed as an absolute change and not a relative change) in the cure rate between the two arms will be presented along with 95% two-sided CI based on a stratified analysis using Cochran-Mantel–Haenszel (CMH) weights. For the statistical analysis, BU categories I-III will be the three strata. The difference in cure rate between the two treatment groups (RC8 *vs.* RCA4) and the corresponding 95% CI will be calculated. Treatment with RCA4 will be declared non-inferior to treatment with RC8 if the lower bound of a two-sided 95% confidence interval (CI) for the difference in cure rates (expressed as an absolute change and not a relative change) between the two treatment arms is greater than − 10%. A superiority hypothesis will be tested once non-inferiority is proven. Superiority can be concluded if the lower bound of a two-sided 95% confidence interval for the difference in cure rates (expressed as an absolute change and not a relative change) between the two treatment arms is greater than 0%. Details for analysis of secondary efficacy outcomes will be included in the Statistical Analysis Plan (SAP).

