#### Randomization

Each patient will be assigned a unique study code number, kept by the site Clinical PI and the clinical site study coordinators. Data relevant for randomization will be sent by email to the randomization manager at the Data Management and Monitoring Centre (DMMC) at Instituto de Salud Carlos III (ISCIII). The DMMC team generates the random sequence upon receiving the information from the clinical sites, i.e. patient code and category of the lesion. Participants are randomly assigned to either control or experimental group as per a computer-generated randomization schedule stratified by site using permuted blocks of random sizes (*n* = 4). Blocked randomization assures generation of study groups with the same size, and a close balance on the numbers in each group by site at any time during the trial. The random sequence is generated in an Excel spreadsheet via Random.org.

Data for randomization will be sent by text (SMS) where it is not possible to send by email. After computer-generated random allocation to either RC8 or RCA4, the randomization group will be provided by email to the site Clinical PI and the clinical site study coordinators. Randomization will be stratified by lesion categories I, II, or III, using a fixed block size within each strata. The target sample size is based on confirmation of *M. ulcerans* infection by polymerase chain reaction (PCR), which will be assessed after the randomization process.

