### Endpoints of the study

#### Definitions of the populations for analysis

Intention-to-Treat Exposed (ITT-E): this population will consist of all randomized patients who receive at least one dose of randomized study medication. Patients will be assessed according to their randomized treatment, regardless of the treatment they receive.Per Protocol (PP): this population will consist of subjects in the ITT-E population who complete the study and are not major protocol violators.Per Protocol (PP) PCR-positive population: The PP PCR-positive population includes those randomized patients with a clinical diagnosis of very likely BU or likely BU, PCR-positive, and with no major violations of the protocol. Unless stated otherwise, the PP PCR-positive population will be used for efficacy analyses.Intention-to-Treat Exposed (ITT-E) PCR-positive population: The ITT-E PCR-positive population includes those randomized patients with a clinical diagnosis of very likely BU or likely BU, PCR-positive that have, at least, taken one dose of the study drugs. This population might include major violators of the protocol. The ITT-E PCR-positive population will be also used for secondary analysis of efficacy.Per Protocol (PP) Clinical Diagnosed (CD) population: The PP CD population includes those randomized patients with a clinical diagnosis of very likely BU or likely BU and with no major violations of the protocol. This population includes both PCR-positive and PCR-negative. The PP CD population will be also used for secondary analysis of efficacy.Intention-to-Treat Exposed (ITT-E) Clinical Diagnose (CD) population: The ITT-E CD population includes those randomized patients with a clinical diagnosis of very likely BU or likely BU that have, at least, taken one dose of the study drugs. This population might include both PCR-positive and PCR-negative and major violators of the protocol. The ITT-E CD population will be also used for secondary analysis of efficacy.Safety: The Safety Population (SP) is defined as all subjects who receive at least one dose of randomized study medication. Subjects will be analysed according to the actual treatments received. Unless otherwise stated, the SP will be used for safety analyses.Pharmacokinetic (PK): the PK population is defined as the participants in the SP who receive at least one dose of randomized study medication and have at least one evaluable PK sample. Participants will be analysed according to the treatment actually received.

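### The per-protocol PCR-positive set alone decides non-inferiority and, by default, superiority; the randomised PCR-positive set is secondary and need not agree

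*Protocol article*

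**What the plan says.** The per-protocol (PP) PCR-positive set is fixed in three places in the protocol article.

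- **Primary endpoint:** cure is assessed "12 months after treatment initiation, in the PP PCR-positive population".
- **Efficacy analysis:** "Primary efficacy analysis will be determined for the PP PCR-positive population".
- **Definitions of the populations for analysis:** "Unless stated otherwise, the PP PCR-positive population will be used for efficacy analyses".

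The Efficacy analysis section declares non-inferiority if the lower limit of the two-sided 95% interval for the difference in cure rates lies above −10%. It then adds: "A superiority hypothesis will be tested once non-inferiority is proven", with 0% as the limit. No population is named for that step, so the default applies.

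Of the randomised counterpart the definitions say: "The ITT-E PCR-positive population will be also used for secondary analysis of efficacy". The secondary endpoints repeat the 12-month cure rate in the ITT-E PCR-positive, PP clinically diagnosed and ITT-E clinically diagnosed sets. None of these enters the decision rule.

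The generic PP set is "subjects in the ITT-E population who complete the study and are not major protocol violators". The PP PCR-positive definition mentions only the absence of major violations. The sections on discontinuation of study medication and on withdrawal both say that the patients concerned will be analysed, without naming the analysis.

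**The concern.** Major violations, and completion where it is required, arise after randomisation and can be influenced by the allocated regimen. A PP comparison is then no longer a comparison of randomised groups. The protocol article contains three features that could make exclusions differ between arms:

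- Study treatment lasts 8 weeks in RC8 and 4 weeks in RCA4, so the time at risk of non-compliance or discontinuation differs.
- Under Laboratory evaluation, the week-4 pregnancy test applies to RC8 only, and a positive result ends trial participation.
- The trial is open-label and local clinicians follow patients unblinded.

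The restriction to PCR-positive patients is not the problem. PCR confirmation is something "which will be assessed after the randomization process", but if it rests on the diagnostic samples taken at entry, as the Microbiological analysis section suggests, the allocated regimen cannot affect it. The ITT-E PCR-positive set therefore keeps the randomised comparison in the patients of interest.

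At stake is the headline claim. With so few failures expected, the classification of a handful of patients can decide whether RCA4 is called non-inferior. For superiority, a PP set offers no protection, because selective exclusion can itself create a difference.

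**Working it through.** **1. The plan's own sample size.** Inputs from the Sample size section: cure 95.9% in both arms, margin 10 points, one-sided alpha 2.5%.

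n per arm = (z_α + z_β)² × 2p(1−p) / margin²

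- 80% power: (1.960 + 0.842)² × 2 × 0.959 × 0.041 / 0.01 = 61.7, so 62.
- 90% power: the same formula gives 82.6, so 83.
- Allowing for 5% loss: 62/0.95 gives 66; 66/0.95 (PCR confirmation) gives 70.

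These match the article, which says "so 66 PCR-confirmed patients are needed in each arm (or 132 in total) to achieve the required 62 evaluable patients". Expected failures per arm are 62 × 0.041 = 2.5.

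**2. How few patients decide non-inferiority.** Unstratified Wald lower bound = d − 1.96 × √[p_T(1−p_T)/n_T + p_C(1−p_C)/n_C], with d = RCA4 minus RC8. The counts are illustrations.

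| RCA4 cured | RC8 cured | d | SE | Lower bound | Result |
|---|---|---|---|---|---|
| 60/66 | 63/66 | −4.5% | 4.37% | −13.1% | fails |
| 60/63 (three RCA4 failures removed) | 63/66 | −0.2% | 3.71% | −7.5% | passes |
| 62/66 | 63/66 | −1.5% | 3.90% | −9.2% | passes |
| 62/66 | 63/63 (three RC8 failures removed) | −6.1% | 2.94% | −11.8% | fails |

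Three exclusions reverse the conclusion in either direction. Near the limit, one patient is enough: at 62 per arm with 3 failures in RC8, RCA4 passes with 4 failures (−9.7%) and fails with 5 (−11.9%).

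**3. Superiority.** By the same formula, 61/62 in RCA4 against 57/62 in RC8 gives d = 6.5%, SE = 3.81% and a lower bound of −1.0%, so superiority is not shown. Removing the single RCA4 failure gives 61/61 against 57/62, d = 8.1%, SE = 3.46% and a lower bound of +1.3%, so superiority would be declared.

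**4. What the ITT-E requirement costs if missing outcomes count as failures.** With the planned 5% loss scored as failure, cure in each arm is 0.95 × 95.9% = 91.1%. At 66 per arm, SE = √(2 × 0.911 × 0.089 / 66) = 4.96%. Power = Φ(10/4.96 − 1.96) = Φ(0.06), about 52%. The rule for missing outcomes therefore matters a great deal.

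The planned analysis uses Cochran-Mantel-Haenszel weights over lesion category, which would shift the exact cut-offs slightly.

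**The case against.** A PP set has a recognised place in non-inferiority, since keeping non-adherent patients can dilute a true difference. The ITT-E results will be reported, and multiple imputation is planned as a sensitivity analysis, so disagreement would be visible. The Treatment section says all treatment is supervised, by admission or direct observation, which limits non-compliance. What counts as a major violation, and who classifies it, is ordinary SAP content. All of this stands. It supports keeping PP PCR-positive in the decision, but not letting it decide alone.

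A reader might go further and infer that the plan favours RCA4. The documents do not support that. The longer RC8 course and the RC8-only pregnancy test both suggest more exclusions from RC8. If those excluded were failures, non-inferiority and superiority would be harder to show, as the last row of the table illustrates. Nor does the article make treatment failures major violators: rapid lesion enlargement is listed as a reason to stop study medication, and the same section says those patients are analysed.

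A reader might also infer a loss of power because the 5% allowance covers only loss to follow-up. The article gives no violator rate, so no such loss can be put in figures.

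**Conclusion.** The concern holds as a weakness in the decision rule: a single set, selected after randomisation, decides both claims, and the analysis that preserves randomisation has no say. Superiority is the clearer fault, because a PP set is not conservative for that claim. For non-inferiority the fault is only that agreement is not required.

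The direction of any bias is unknown. Its possible size is shown by the illustrations: three exclusions move the lower bound by 5.6 points one way (−13.1% to −7.5%) or 2.6 points the other (−9.2% to −11.8%), across a −10% limit. They assume that the excluded patients are failures and all come from one arm, and they use unstratified intervals. Unequal exclusion is a risk that the design creates, not something the documents report.

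This should be fixed before analysis. It does not invalidate the design, since the ITT-E analysis is already planned and the sample size reproduces.

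**What to change.** 1. Efficacy analysis: state that superiority is tested in the ITT-E PCR-positive population.
2. Efficacy analysis: keep PP PCR-positive for non-inferiority, but declare it only if the ITT-E PCR-positive analysis also has a lower limit above −10%. In that ITT-E analysis, handle missing 12-month outcomes by the multiple imputation already planned for sensitivity analyses.
3. Discontinuation and withdrawal sections: name the analysis in which those patients are included, and reconcile this with the PP definitions. Say also whether the requirement to complete the study, stated only for the generic PP set, applies to PP PCR-positive.

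The cost is a few sentences, with no new data and no new analysis population; recruitment already runs until 66 PCR-confirmed patients per arm are randomised. The drawback is some loss of joint power, because both analyses must succeed. Its size depends on the rule for missing outcomes. Counting the lost 5% as failures would cut ITT-E power to about 52% at 66 per arm, so that rule should not be the deciding one, though it can be reported as a sensitivity analysis.

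### With the usual intervals for a difference in cure rates, 62 and 83 evaluable patients per arm do not deliver both the stated 2.5% one-sided error and the stated 80% and 90% power

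*Protocol article*

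**What the plan says.** The Sample size section of the protocol article assumes a cure rate of 95.9% among PCR-confirmed patients in both arms, a "10% non-inferiority margin" on the negative side, and a "2.5% one-sided alpha level". From these it derives 62 evaluable patients per arm for 80% power. For the possible extension it states: "For 90% power, based on the assumptions above, the study would require data from 83 evaluable PCR-confirmed patients per treatment arm". Allowance for loss is then added: "It is estimated that 5% of PCR-confirmed patients will be lost-to-follow-up, so 66 PCR-confirmed patients are needed in each arm".

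The Efficacy analysis section sets the primary analysis. The absolute difference in cure rate is "presented along with 95% two-sided CI based on a stratified analysis using" Cochran-Mantel–Haenszel (CMH) weights, with BU categories I to III as strata. Non-inferiority is declared if the lower bound of the two-sided 95% interval lies above −10%. The section fixes the weights, strata, confidence level and margin. It gives no variance estimator or interval method, and its deferral to the SAP covers only the secondary efficacy outcomes.

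**The concern.** At 95.9% cure, 62 patients give 62 × 0.041 = 2.5 expected failures per arm, divided over three strata. With so few failures the Wald variance behaves badly. When the experimental arm happens to have few failures, the estimated difference looks good and its estimated standard error shrinks as well, so the lower bound clears −10% too easily. A sample size from the same approximation carries the same optimism.

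What is at stake is the primary decision on a halved antibiotic course. Depending on the interval used, either the chance of wrongly declaring non-inferiority is above the stated 2.5%, or the chance of showing non-inferiority when the regimens are equal is well below the stated 80% or 90%.

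**Working it through.** **Inputs.** From Sample size: cure 0.959 in both arms, margin 0.10, one-sided alpha 0.025, n = 62 or 83 evaluable per arm, 66 or 88 before loss. From Efficacy analysis: non-inferiority if the lower 95% bound exceeds −0.10. From General considerations: 91.3% as the lower quartile of the standard arm's cure rate. The category mix and the cure rate by category are not given.

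**Step 1: reproduce the plan.** Unpooled normal formula: n = (z₁₋α + z₁₋β)² × 2p(1−p) / margin².
- 80%: 7.849 × 2 × 0.959 × 0.041 / 0.01 = 61.7, so 62.
- 90%: 10.507 × 0.078638 / 0.01 = 82.6, so 83.
- Inflation: 62/0.95 = 65.3 (66) and 66/0.95 = 69.5 (70); 83/0.95 = 87.4 (88) and 88/0.95 = 92.6 (93).

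All the stated figures reproduce, so the design rests on the Wald approximation.

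**Step 2: why it is optimistic.** The formula uses the standard error at equal rates: √(0.078638/62) = 0.036. At the margin (85.9% against 95.9%) it is √[(0.859 × 0.141 + 0.959 × 0.041)/62] = √(0.160438/62) = 0.051. Score intervals use a variance restricted to the margin; Wald intervals do not.

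**Step 3: exact operating characteristics, unstratified.** For each rule, the binomial probabilities of all outcome pairs that lead to a declaration of non-inferiority are summed. Error is at 85.9% (RCA4) against 95.9% (RC8); power is at 95.9% in both.

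| n per arm | Wald: error / power | Miettinen-Nurminen: error / power | Newcombe: error / power |
|---|---|---|---|
| 62 | 4.16% / 80.8% | 2.32% / 65.2% | 2.33% / 65.2% |
| 66 | 3.50% / 80.5% | 2.08% / 69.3% | 2.46% / 69.9% |
| 83 | 3.71% / 89.3% | 2.09% / 79.0% | 2.14% / 79.0% |
| 88 | 3.78% / 91.6% | 2.07% / 81.4% | 2.29% / 81.4% |

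Other rules do not reach both targets at 62 either. Agresti-Caffo gives 2.70% / 72.9% and continuity-corrected Wald 1.62% / 65.0%. Wald with a critical value of 2.31 gives 1.97% / 70.7% at these rates, but its error rises to 4.55% at other control rates.

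**Step 4: dependence on the control rate.** Wald error at 62 per arm is 3.2% if control cure is 91.3% and 5.4% if it is 99%. Over control rates of 90% to 99% and the four sizes in the table it runs from about 2.8% to 6.1%. Only in the limit of 100% control cure does it go much higher (9.3% at 66). Over 90% to 100%, Miettinen-Nurminen stays at or below 2.5% and Newcombe at or below about 2.6%.

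**Step 5: effect of stratification.** Simulation with 400,000 runs per scenario, 62 per arm, four assumed category mixes and three assumed sets of cure rates by category: the CMH-weighted interval with Wald, n−1 or Sato variance has error of 4.0–4.6% and power of 79–88%. With equal cure in all categories these are 4.2% and 81%. Stratification therefore does not remove the problem. The 88% comes from a mix whose average cure exceeds 95.9%.

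**Step 6: size for the stated power.** Exact power passes 80% at about 84 per arm (Newcombe) to 86 (Miettinen-Nurminen), and 90% at about 107 to 109. The asymptotic Farrington-Manning formula gives about 90 for 80%.

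**Step 7: what it means for a result.** At 62 per arm, unstratified, with 0, 1, 2 or 3 failures on RC8, Wald accepts up to 2, 3, 3 or 4 failures on RCA4. Score and Newcombe accept up to 1, 2, 2 or 3. One patient separates the verdicts.

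**The case against.** The strongest reply is that the protocol never says the CMH-weighted interval uses a Wald variance. CMH weights can equally go with a stratified score or Newcombe interval, and the choice may stand in the SAP, which is not shown. That is correct. A reader might infer that the trial will wrongly declare non-inferiority about 1.7 times as often as stated (4.16/2.5). The document does not support that as a fact: it holds only for a Wald or Sato interval. Nor may the inflated error and the lost power be added together; they are alternatives.

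Second, 62 and 83 are not arithmetic errors. A standard formula was applied correctly, and both figures reproduce.

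Third, 4.2% and 65% are points on a discrete, jagged curve. Recruitment runs to at least 66 PCR-confirmed patients per arm, so the analysed number may differ from 62; at 66 the Wald error is 3.5% and score or Newcombe power 69–70%. The stratified results also rest on invented category mixes.

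These replies limit how firmly any single figure may be stated. They do not restore the stated pair. The Sample size section asserts 2.5% error together with 80% or 90% power, and none of the interval methods checked gives both at 62. Leaving the interval formula to the SAP does not help, since a choice that holds the error makes the published power wrong.

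**Conclusion.** The point holds in conditional form. The sizes of 62 and 83 come from a Wald approximation that is optimistic with about 2.5 expected failures per arm at 62. With a Wald-type or Sato interval, one-sided error is about 4.2% at 62 and 3.7% at 83 (roughly 3–6% over control rates of 90–99%). With a score or Newcombe interval the error is about 2.1–2.3% at those sizes, and power is about 65% at 62, 69–70% at 66 and 79% at 83. The shortfall against the stated power is then about 15 points at 62 and 11 points at 83.

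These figures assume the protocol's own 95.9% cure and 10-point margin, and are exact for an unstratified comparison. Stratified values depend on the unknown category mix. It is not established which interval the trial will use, so neither the raised error nor the lost power can be called the trial's actual property.

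**What to change.** Before outcome data are seen, add to Efficacy analysis (and the SAP, if it does not already say so) that the primary interval is the stratified Miettinen-Nurminen score interval, or the stratified Newcombe interval, with CMH weights over BU categories I to III. State the contrast as RCA4 minus RC8, because the present text writes RC8 first while judging a lower bound against −10%.

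In Sample size, restate power for that interval: about 65% at 62 evaluable per arm and about 79% at the 83 already foreseen as the extension. Add that about 84–86 would be needed for 80% and about 107–109 for 90%. Mark these as unstratified figures, and check them by simulation with a stated category mix.

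The change to the text needs no extra patients or data. Its cost is a less favourable stated power. Recovering 80% does cost patients: 84–86 evaluable per arm instead of 62, which is slightly beyond the planned extension.
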